### Data analysis

Continuous data will be expressed using mean and standard deviation or median and interquartile range, according to their statistical distribution. The normality assumption will be studied using the Shapiro-Wilk test.

The relationship between chronological age and BA will be investigated using correlation and concordance coefficients (Lin for continuous data and Cohen’s kappa for categorical data), Bland and Altman plot and approaches based on non-linearity assumptions. The difference between BA and chronological age will be expressed as a difference and as a percentage (ratio) to assess the relevance of these two modalities.

The relationship between BA, difference between BA and chronological age and frailty will be analyzed using correlation coefficients (Pearson or Spearman, depending on the statistical distribution) and mediation analysis.

A detailed description of frailty will be carried out. First, frailty will be treated as an ordinal variable. Then, frailty will be categorized according to statistical distribution and to data reported in the literature. Likewise, age (BA and chronological age) will be considered as a continuous variable and then as a categorical variable with groups defined according to their clinical relevance and statistical distribution. The relationships will be analyzed using the Chi-square test or Fisher’s exact test (categorical x categorical) and the analysis of variance or Kruskal-Wallis test if the assumptions of the analysis of variance are not met (categorical x continuous).

For longitudinal analyses, mixed models will be used to analyze the relationship between BA, difference between BA and chronological age, and temporal changes of level of frailty, taking into account between and within patient variability (patient as random-effect). The evolution of frailty will be also assessed by trajectory modelling. The relationship between trajectories and the difference between BA and chronological age will be analyzed using analysis of variance or Kruskal-Wallis test. Multivariate analyses will be carried out to take into account confounding factors selected according to univariate results and to their clinical relevance. A particular attention will be paid to multicollinearity. Center will be considered as random-effect. The results will be expressed with effect sizes and 95% confidence intervals. Sensitivity analyses will be proposed in order to study the statistical nature of the missing data and to propose the most appropriate imputation method.

The relationships between BA, difference between BA and chronological age, individual frailty and quality of life will also be investigated.

Tolerance criteria (actual dose received, discontinuation of TKI due to intolerance, adverse events, TKI changes and number of TKI lines) will be the subject of detailed descriptive analysis. Then, marginal Cox model with time-dependent variables and joint models for longitudinal data will be used to analyze the impact of BA, difference between BA and chronological age, and individual frailty on tolerance to TKIs and therapeutic response. The proportional hazards hypothesis will be tested using the Schoenfeld test and residual plot. Death will be treated as a competitive risk using Fine and Gray model. Multivariate analyses will be performed to take account of possible confounding factors (e.g. sex, age, Sokal and ETLS scores, hemoglobin, platelets, leukocytosis, splenomegaly, type of treatment).

Statistical analyses will be carried out using Stata software (version 15, StataCorp, College Station) for a two-tailed type I error at 5% applying when appropriate a Sidak’s correction for multiple comparisons.

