### Study objectives and endpoints

#### Main objective and endpoint

The main objective of the study is to evaluate the value of combining BA determination with individual fragility assessment to personalize the management of CML patients treated with TKI, in terms of tolerances.

The first primary endpoint is the difference between BA and chronological age (of the CML clone and non-malignant cells in the same patient) expressed as a difference and as a percentage (ratio).

The second endpoint is the individual frailty assessed using G-CODE score, Rockwood Frailty Scale and Charlson Comorbidity Index.

And the last endpoint is the TKI tolerance in patients with CML assessed by actual dose received, TKI discontinuation due to intolerance, TKI discontinuation due to adverse events, TKI changes due to intolerance and number of TKI lines.

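### The ANOVA-or-Kruskal-Wallis rule offers no test that tolerates unequal spread, which the difference or the ratio form of biological age will show when the compared groups differ in age

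*Protocol article*

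**What the plan says.** The protocol article defines the first primary endpoint (Main objective and endpoint) as the gap between biological age (BA) and chronological age (CA), in two forms. Data analysis repeats that the gap "will be expressed as a difference and as a percentage (ratio) to assess the relevance of these two modalities".

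For frailty, the section starts from an ordinal variable. After that, "frailty will be categorized according to statistical distribution and to data reported in the literature". BA and CA are likewise to be cut into groups. Continuous variables are then compared across groups by "the analysis of variance or Kruskal-Wallis test if the assumptions of the analysis of variance are not met (categorical x continuous".

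For the longitudinal part it says: "The relationship between trajectories and the difference between BA and chronological age will be analyzed using analysis of variance or Kruskal-Wallis test".

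No test that allows unequal variances is named. The one assumption check stated near these tests is "The normality assumption will be studied using the Shapiro-Wilk test", and it concerns normality.

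**The concern.** Classical ANOVA pools the group variances and so assumes that they are equal. The text sends any failure of ANOVA's assumptions, including this one, to Kruskal-Wallis. As a test of location, Kruskal-Wallis also misses its nominal level when spread and group size both differ. Neither branch of the rule therefore covers that case.

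This would be a routine remark in most studies. Here it has a specific cause: the endpoint is carried in two forms that differ by division by age, and patients are adults from 18 with no upper age limit stated. If one form has the same spread at every age, the other does not. A small frail group or a small trajectory class could then be compared at a real error rate above or below 5%, and the rate could differ between the two forms of the same endpoint.

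**Working it through.** **1. The protocol's own figure.** Sample size states power above 80% for an effect of 0.5 SD with 200 patients, 45% of them frail or pre-frail, at two-sided 0.01. With groups of 110 and 90, the standard error is √(1/110 + 1/90) = 0.142, so 0.5/0.142 = 3.52 and 3.52 − 2.576 = 0.94. Power is Φ(0.94) = 0.827. The figure reproduces. The formula assumes equal variances.

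**2. Why both forms cannot have constant spread.** Write D = BA − CA and R = BA/CA. Then R − 1 = D/CA, so SD(R | CA) = SD(D | CA)/CA. If SD(D | CA) is proportional to CA^g, SD(R | CA) is proportional to CA^(g−1).
- g = 0, with an SD of D of 6 years: the SD of R is 6/50 = 12% at age 50 and 6/75 = 8% at age 75.
- g = 1, with an SD of R of 10%: the SD of D is 5 years at 50 and 7.5 years at 75.
- At g = 0.5 both vary.

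**3. Assumptions not in the documents.** An SD of about 6 years or 10%; mean ages of 50 and 65 for two frailty groups, or 50, 62 and 75 for three; and the three-group splits. The mean of D is zero in every group, so both forms share the same true null.

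**4. Simulated rejection rates, nominal 5%, no true effect** (2,000 to 5,000 runs per cell; Monte Carlo error about 0.3 to 0.5 points).

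| Groups | Form with unequal spread | ANOVA | Kruskal-Wallis |
|---|---|---|---|
| 110/90, same age distribution | neither | 4.6-5.5% | 4.6-5.5% |
| 110/90, ages 50/65 | ratio (g = 0) | 4.1-4.2% | 4.9-5.0% |
| 110/90, ages 50/65 | difference (g = 1) | 5.9-6.4% | 5.4-5.5% |
| 177/144 (n = 321) | ratio (g = 0) | 4.5% | 4.7% |
| 177/144 | difference (g = 1) | 5.2% | 5.2% |
| 110/70/20 | ratio (g = 0) | 1.9-3.0% | 3.0-3.8% |
| 110/70/20 | difference (g = 1) | 9.6-9.9% | 6.7-7.2% |
| 177/112/32 (n = 321) | ratio (g = 0) | 2.1% | 3.2% |
| 177/112/32 | difference (g = 1) | 9.2% | 6.9% |

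The form with equal spread stayed at about 4-6%. Welch's ANOVA stayed at about 4-6% for both forms throughout. Other runs at n = 321 and 55/35/10%, with frailty correlated 0.4 to 0.6 with age, gave 7.3-10.5% (ANOVA) and 6.2-7.6% (Kruskal-Wallis) for the difference. For the ratio they gave 2.1-3.1% and 3.2-4.6%.

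**5. Why the small group drives it.** In the 110/70/20 case with g = 1, the group SDs of the difference were 5.12, 6.29 and 7.46.
- Pooled variance ≈ (110 × 26.2 + 70 × 39.6 + 20 × 55.7)/200 = 33.8, so the pooled SD is 5.8.
- The smallest group's true SD is 7.46/5.8 = 1.29 times what ANOVA credits it with, so the test is liberal.
- With g = 0, the SDs of the ratio were 13.29, 10.28 and 8.28. The pooled SD is √[(110 × 176.6 + 70 × 105.7 + 20 × 68.6)/200] = 11.9, and 8.28/11.9 = 0.70, so the test is conservative.

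For 110/90 with SDs of 13.29 and 9.74, the true variance of the mean difference is 176.6/110 + 94.9/90 = 2.66. The pooled version is [(110 × 176.6 + 90 × 94.9)/200] × (1/110 + 1/90) = 2.82. The standard errors differ by a factor of only √(2.66/2.82) = 0.97, which is why the near-even split is harmless.

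**6. Age groups.** If either form is compared across CA groups, the age gap is there by construction. With assumed groups of 32/128/161 at mean ages 30/55/75 and g = 0, the ratio was rejected in 21.5% (ANOVA) and 11.1% (Kruskal-Wallis). With sizes 161/128/32 the rates were 1.7% and 2.7%, and with about 67 per group 6.5% and 6.3%.

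**The case against.** ANOVA with a Kruskal-Wallis fallback is conventional, and the document is a condensed article whose analysis plan may refine it. The only split the protocol states is 45/55, where nothing of note happens. The marked departures need a small extreme group and age gaps that the documents do not give. These comparisons are also a supporting step: correlations, mediation analysis, mixed models, Cox and joint models with effect sizes and confidence intervals carry most of the inference.

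Most of this stands and sets the priority low. It does not remove the point. The article names the fallback, so this is a stated choice and not an omitted detail. The 45/55 figure belongs to the power calculation and does not bind the analysis, where frailty cut-points depend partly on the observed distribution and trajectory classes have no fixed size.

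Three stronger readings are tempting, and the documents do not support them.
- **That unequal spread must occur, so the two forms are always tested at different error rates.** It needs groups that differ in age. That holds by construction for age groups and is plausible for frailty groups and trajectory classes, but is stated nowhere. A real shift in error rate also needs unequal group sizes.
- **That Shapiro-Wilk decides between the two tests.** In the text it follows the choice of descriptive summary. The ANOVA sentence refers to that method's assumptions without naming a check or a threshold.
- **That the relevance of the two forms will be judged by these p-values.** The phrase on relevance stands with the agreement analyses of BA against CA, and the trajectory sentence names the difference only.

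**Conclusion.** The point holds as a small, conditional one. The stated rule has no branch that keeps its level as a location test when spread and group size both differ, and the algebra of the endpoint makes unequal spread in at least one form the expected result wherever the compared groups differ in chronological age.

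Under the assumed 55/35/10% split, the distortion is a rate of roughly 7-10% for the difference or roughly 2-5% for the ratio. These come from two alternative scenarios for how BA error scales with age, so they are not to be read as occurring together. Direction and size rest on group sizes, age gaps and that scaling, none of which the documents give. Under the protocol's 45/55 split the effect is negligible. The stated sample size and power stand, and the mixed, Cox and joint models are untouched. It is a cheap improvement to a supporting analysis.

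**What to change.** For every categorical-by-continuous comparison of BA, the difference and the ratio, including the trajectory comparison, name one primary test that allows unequal variances: Welch's ANOVA, or linear regression with heteroscedasticity-robust (HC3) standard errors. Use it from the start, without a preliminary check, and report Kruskal-Wallis as a sensitivity analysis. The regression route also gives the effect sizes and 95% confidence intervals that the section promises, which Kruskal-Wallis does not give directly.

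The cost is a sentence in the analysis plan and, for the regression, an option in the software already named. When variances are equal the loss of power is negligible. Data collection, sample size and procedures do not change.

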### Sample size

The sample size in order to study the relationship between BA, individual frailty and tolerance to TKIs will be estimated according to Hanlon P. et al. [19], Huan-Tze L. et al. [20] and the data from CML Observatory.

Considering 45% frail and pre-frail patients, an effect size greater than 0.5 (moderate to large according to Cohen’s rules of thumb) between BA and individual frailty can be highlighted with 200 patients, for a two-sided type I error at 0.01 (correction due to multiple comparisons) and statistical power above 80%. An interim analysis is planned at inclusion of 100 patients to estimate statistical power according to observed effect sizes and 95% confidence intervals.

Furthermore, given the data reported in the literature [21] and data from CML Observatory, it seems reasonable to expect 35% TKI intolerance. Thus, an enrolment of 321 patients will enable us to identify a 15% absolute difference in intolerance (treated as censored data) for a two-sided type I error of 5% and statistical power of 80%, which correspond to a reasonable hazard ratio of at least 1.4.

An interim analysis is planned at inclusion of 100 patients to re-estimate statistical power according to observed effect sizes and 95% confidence intervals for the relationship between BA and individual frailty.

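### Comparing BA minus age across frailty trajectories by ANOVA or Kruskal-Wallis treats modelled classes as error-free, which shrinks the class difference in this supplementary analysis

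*Protocol article*

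**What the plan says.** The Data analysis section of the protocol article gives two routes to the longitudinal relation between BA and frailty. The first is regression: "mixed models will be used to analyze the relationship between BA, difference between BA and chronological age, and temporal changes of level of frailty", with patient as a random effect. The second is an addition: "The evolution of frailty will be also assessed by trajectory modelling". For that second route the test is named: "The relationship between trajectories and the difference between BA and chronological age will be analyzed using analysis of variance", with Kruskal-Wallis as the alternative. The type of trajectory model, the number of classes and the rule for assigning patients to classes are not given.

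The next sentence deals with adjustment: "Multivariate analyses will be carried out to take into account confounding factors selected according to univariate results and to their clinical relevance". Centre is a random effect, and results are to be reported as effect sizes with 95% confidence intervals. Chronological age is not named there. It is named further down, in the list for the tolerance and response models: "possible confounding factors (e.g. sex, age, Sokal and ETLS scores, hemoglobin, platelets, leukocytosis, splenomegaly, type of treatment".

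The age-acceleration measure is the raw contrast: "The difference between BA and chronological age will be expressed as a difference and as a percentage (ratio".

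By the Intervention section and Table 2, frailty is scored at inclusion, M6, M12, M24 and M36. Blood for BA is drawn at diagnosis, M3 and M12. The section on determining biological age assigns the diagnosis sample to malignant cells and the two later samples to non-malignant cells.

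**The concern.** A trajectory model estimates class membership; it does not observe it. Neither named test, in its standard form, accepts a probability of membership, so naming the test implies that each patient receives one label which is then treated as fact. With five frailty scores at most, some labels will be wrong. If the errors are unrelated to BA acceleration, each assigned class is a mixture of the true classes, and the difference between them shrinks. The intervals are then centred on the wrong value and ignore the uncertainty in the labels. Effect sizes and intervals are exactly what the section promises to report.

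A second, smaller issue concerns age. The raw difference between BA and chronological age is itself correlated with age unless BA rises by exactly one year per year of age. If the classes differ in age, a one-way test can show a difference, or hide one, for that reason alone.

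At stake is a null or weak trajectory result that could be misread as contradicting the mixed models.

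**Working it through.** **Inputs from the article.** Sample size section: "Considering 45% frail and pre-frail patients", effect size 0.5, 200 patients, two-sided alpha 0.01, power above 80%; total enrolment 321. These planning figures are not tied to trajectories and serve here only as a reference scale.

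**Assumptions, not in the article.** Two classes; a 45% class borrowed from the frailty share; symmetric classification error e of 5% to 25%, unrelated to BA acceleration; within-group SD of 1. For age: slope b of BA on age 0.7 to 1.0, age gap between classes 5 to 15 years, SD of BA minus age 5 years.

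**1. The plan's own figure.** With groups known without error, power = Φ(d·√(N·q·(1−q)) − 2.576), where q is the group share. For d = 0.5, N = 200, q = 0.45: 0.5 × √(200 × 0.45 × 0.55) = 3.518, and 3.518 − 2.576 = 0.942, so power is 82.7% (81.9% by the noncentral t). The stated power above 80% reproduces. At N = 321 it is 97.0%.

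**2. Attenuation.** The observed difference is d·λ, with λ = PPV + NPV − 1. For e = 10% and true share 0.45:
- PPV = 0.405 / (0.405 + 0.055) = 0.880
- NPV = 0.495 / (0.495 + 0.045) = 0.917
- λ = 0.797, so 0.50 SD becomes 0.40 SD.

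The assigned share is q = 0.45(1−e) + 0.55e, used in the power formula above. Coverage of the naive 95% interval at N = 321 is Φ(1.96 − k) − Φ(−1.96 − k), where k = (0.5 − 0.5λ)/SE and SE = 1/√(321·q·(1−q)), about 0.112.

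| Error | λ | Observed d | Power, N=200 | Power, N=321 | Coverage, N=321 |
|---|---|---|---|---|---|
| 5% | 0.898 | 0.45 | 72% | 92% | 93% |
| 10% | 0.797 | 0.40 | 59% | 84% | 85% |
| 15% | 0.696 | 0.35 | 45% | 70% | 73% |
| 20% | 0.596 | 0.30 | 32% | 54% | 56% |
| 25% | 0.496 | 0.25 | 21% | 36% | 38% |

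Power is at alpha 0.01. A smaller class fares worse: with a 20% class and 10% error, λ = 0.665, d = 0.33, and power is 30% at N = 200 and 52% at N = 321.

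**3. Check by simulation.** A two-class linear trajectory model was fitted by EM, with patients assigned to their most probable class (five visits, N = 321, true d = 0.5, 400 runs per scenario). At 95%, 89% and 83% correct classification, the mean estimates were 0.46, 0.39 and 0.33, and coverage was 92%, 83% and 68%. This agrees with the formula. At 72% and 62% correct, the estimates were 0.23 and 0.13, with coverage of 34% and 13%.

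**4. Age.** With no true effect, the class difference in raw BA minus age is (b − 1) × age gap. For b = 0.8 and a 10-year gap it is −0.2 × 10 = −2 years, or −0.4 SD. Across the assumed range it runs from 0 (b = 1.0) to −0.3 × 15 = −4.5 years.

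**The case against.** Several points on the other side stand.

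- **Age.** A reader might infer that the plan leaves chronological age unadjusted. The document does not support that: the sentence directly after the named test plans multivariate analyses, and selection by clinical relevance could bring age in. What remains is that age is not fixed there, its entry depends partly on univariate results, and the one-way test itself cannot carry it.
- **Role of the analysis.** The mixed models come first, need no class assignment and can carry covariates. Tolerance, the main objective, is analysed by Cox and joint models with no mention of trajectory classes, and neither sample-size statement refers to trajectories. A reading that the study's main inference is compromised is not supported.
- **Power.** It is tempting to charge the whole loss of power to ANOVA. A separate simulation (assumed 321 patients, 25% class, true difference 0.4 SD, entropy 0.90 / 0.79 / 0.63 / 0.53) gave 81 / 72 / 57 / 47% for the class comparison and 83 / 76 / 63 / 56% for a one-step model. The test itself costs 2, 4, 6 and 9 points; the rest comes from poor class separation, which no method removes. The bias is another matter: the class comparison recovered 92 / 84 / 74 / 67% of the true difference, while the one-step model was close to unbiased.
- **Direction.** Making BA minus age the outcome and trajectory the grouping factor is not an error in itself. The plan speaks of a relationship, and with two classes both directions test the same null.
- **Detail left elsewhere.** The trajectory method and assignment rule may properly sit in the full protocol or analysis plan, so hard assignment is inferred. The test, however, is already named in the article, and it needs labels.

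**Conclusion.** The point holds for a supplementary analysis. Following the named test as written biases the class difference towards zero, provided classification error is unrelated to BA acceleration, and the confidence intervals under-cover. Under the assumed 5% to 25% error and a 45% class, between about 10% and half of the difference is lost. These are illustrations: the article gives no class separation, so no single corrected figure can be derived, and with excellent separation the harm is small. Multivariate models built on the same hard labels keep the same error. The age issue is one of prespecification, and its size rests wholly on the assumed slope and age gap; it vanishes if the slope is 1 or the classes have equal mean age.

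**What to change.** Relate BA minus age to class membership inside the trajectory model (one-step), or use a bias-adjusted three-step method. Prespecify chronological age as a covariate whatever its univariate result. Do this for both the diagnosis (malignant-cell) and the M3/M12 (non-malignant-cell) measures; the baseline value alone would leave out the non-malignant cells, which are part of the primary endpoint. Report classification quality, such as entropy and mean posterior probability by class, and give the association as an odds ratio per year of BA acceleration with its 95% confidence interval. Keep ANOVA or Kruskal-Wallis as description.

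The cost is wording in the analysis plan and somewhat more modelling work. Intervals will be slightly wider, because they reflect the uncertainty in class membership. No new data are needed.

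### Univariate results should not help decide which confounders enter the longitudinal models of biological age and frailty

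*Protocol article*

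**What the plan says.** The Data analysis section of the protocol article has two separate statements on adjustment.

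- **Longitudinal BA–frailty models.** In the paragraph on mixed models and frailty trajectories, the multivariable analyses are to adjust for "confounding factors selected according to univariate results and to their clinical relevance". It then adds "A particular attention will be paid to multicollinearity" and "The results will be expressed with effect sizes and 95% confidence intervals". It states no p-value threshold, no precedence between the two criteria, and no allowance in the intervals for the selection step.
- **Tolerance and response models.** Two paragraphs later: "Multivariate analyses will be performed to take account of possible confounding factors". Examples follow: sex, age, two prognostic scores, blood counts, splenomegaly and type of treatment. No univariate screen is mentioned.

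The BA–frailty relationship is a core part of the study. Under Main objective and endpoint, the gap between BA and chronological age is listed first and individual frailty second. The Sample size section gives this relationship its own calculation: an effect size above 0.5 "can be highlighted with 200 patients, for a two-sided type I error at 0.01 (correction due to multiple comparisons) and statistical power above 80" per cent.

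**The concern.** A univariate screen, as usually applied, asks whether a covariate is associated with the outcome in these data. Confounding is a different property: the covariate must be related to both BA and frailty. A modest confounder can miss any threshold in a few hundred patients, and one whose effect opposes that of BA can look null on its own and still matter once BA is in the model.

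The word joining the two criteria does not settle the matter. If both must be met, a clinically relevant confounder with a null univariate result is dropped. If either is enough, the screen does nothing for confounders already chosen on clinical grounds. The attention to multicollinearity concerns a different problem.

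At stake is the adjusted BA–frailty estimate. A dropped confounder leaves part of its effect in the BA coefficient, and the reported 95% interval is then centred on the wrong value.

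**Working it through.** **1. The plan's own figure.** No stated figure depends on the confounder rule. The BA–frailty calculation does reproduce: 200 patients, 45% frail or pre-frail (90 against 110), effect size 0.5, two-sided alpha 0.01.

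- 0.5 × √(110 × 90 / 200) = 3.518
- 3.518 − 2.576 = 0.942, and Φ(0.942) = 82.7%, in line with the stated power above 80%

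**2. Inputs to the simulations.** The article gives no threshold, confounder strength or covariance, so these are assumptions. All models are linear and cross-sectional, with 3000 replicates per setting.

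*Design A:* eight confounders, each with slope 0.2 on BA and an effect of 0.08–0.15 SD on frailty, no true BA effect, N = 200 or 321.

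| Adjustment | Coverage of 95% CI | Bias (SD per SD) |
|---|---|---|
| Screen at p<0.05 | 79–87% | 0.05–0.09 |
| Screen at p<0.20 | 92.5–95% | 0.02–0.04 |
| All eight kept | 94–96% | about 0 |

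At N = 200 with effect 0.10, the p<0.05 screen kept on average 2.2 of the 8 true confounders. When four of the eight were kept on clinical grounds, coverage was 90–92% at p<0.05 and 94.7–95.4% at p<0.20.

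*Design B:* eight candidate covariates under other assumed structures, with a third option in which the true confounders are kept on clinical grounds.

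| Setting | N | Screen | Coverage, screen only | Bias | Coverage, fixed set | Coverage, screen + clinical |
|---|---|---|---|---|---|---|
| Weak, no BA effect | 200 | 0.05 | 87.5% | 0.062 | 95.2% | 95.2% |
| Weak, no BA effect | 321 | 0.05 | 87.7% | 0.048 | 94.4% | 94.3% |
| Weak, no BA effect | 200 | 0.20 | 95.6% | 0.024 | 94.9% | 94.9% |
| Weak, no BA effect | 321 | 0.20 | 94.9% | 0.017 | 95.1% | 95.0% |
| Weak, BA effect 0.3 | 200 | 0.05 | 95.0% | 0.008 | 93.9% | 94.4% |
| Benign same-direction, no BA effect | 321 | 0.05 | 93.6% | 0.019 | 95.1% | 94.8% |
| Opposing, BA effect 0.3 | 200 | 0.05 | 70.6% | −0.107 | 94.8% | 94.8% |
| Opposing, BA effect 0.3 | 321 | 0.05 | 53.2% | −0.110 | 95.2% | 95.1% |
| Opposing, BA effect 0.3 | 321 | 0.20 | 59.3% | −0.098 | 94.9% | 95.0% |

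In the first two rows the type I error is about 12% against a nominal 5%.

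**3. Bias or narrow intervals?** In design A at N = 200, p<0.05 and effect 0.115, the mean standard error was 0.073, the actual spread of the estimate 0.071 and the bias about 0.08. The half-width is 1.96 × 0.073 = 0.143.

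- With the bias: Φ((0.143 − 0.08)/0.071) − Φ((−0.143 − 0.08)/0.071) = Φ(0.89) − Φ(−3.14) ≈ 81%, close to the simulated value of about 80%.
- Without it: 2Φ(0.143/0.071) − 1 = 2Φ(2.01) − 1 ≈ 96%.

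The standard error is honest for the model fitted, so the loss comes from the omitted confounders.

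**The case against.** The strongest reply is that the rule has two halves. If clinical relevance is enough to keep a factor, the harm largely goes: with the true confounders kept, design B gives 94.3–95.3% coverage. The article does not say which reading applies, nor that the univariate result means association with frailty rather than with BA. This stands, and it means that loss of coverage is possible but not certain. A reader might infer that confounders are picked by p-value alone; the sentence does not say that.

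The size also rests on assumed thresholds and structures. A p<0.20 screen is close to nominal when confounders act in the same direction, and several settings show almost no harm. The simulations are cross-sectional, whereas the plan uses mixed models on repeated frailty measures. These points stand too.

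A reader might infer that the intervals are too narrow in themselves. The screened standard error is smaller than the full-model one (0.075 against 0.088 in design A at N = 200, effect 0.10), but that is because fewer covariates are fitted. Step 3 shows that it is not materially understated.

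A reader might also extend the point to the tolerance models, which serve the main objective. Their sentence names clinical confounders and no screen, so the article does not support that.

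Finally, a condensed article may leave the covariate list to a fuller document. That excuses a missing list. It does not excuse a selection rule that is stated and is open to this criticism.

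**Conclusion.** The point holds for the longitudinal BA–frailty models only. The article lets univariate results in the same data help choose the confounders and does not protect a clinically relevant confounder whose univariate result is null. This can bias the adjusted BA estimate and make its 95% interval under-cover.

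Under the assumed inputs (eight weak same-direction candidates, no BA effect), coverage is about 79–88% with a pure p<0.05 screen and about 92–96% with p<0.20. A fixed set, or a screen with the true confounders kept on clinical grounds, gives about 94–96%. Opposing confounders with a real BA effect did worse, at 53–74% over both thresholds, while other settings showed little or no loss. None of these is a forecast for this study. They show that the rule carries a risk that a fixed set avoids.

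**What to change.** In the sentence on the longitudinal models, delete the reference to univariate results. Suggested wording: *Confounders in the BA–frailty models are fixed before analysis on clinical or causal grounds and are kept whatever their univariate p-values; univariate tables are descriptive.*

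The set should contain at least chronological age and sex, plus baseline variables already collected that plausibly affect both BA and frailty. The tolerance-model list should not be imported whole:

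- Choose between the composite prognostic scores and the separate blood counts, to limit collinearity.
- Include type of treatment, or any other factor arising after baseline, only if it is justified as a confounder. Treatment starts after inclusion and first sampling, so it may lie downstream of baseline status.
- Do not adjust for a component of the frailty measure itself. The G-CODE, for example, includes comorbidity and body mass index.

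**Cost.** The change needs no new data, visits or patients, only a few degrees of freedom and wider intervals. In the simulations at N = 200 the full-set standard error was 0.088 / 0.075 = 1.17 times the screened one in design A (effect 0.10), and 0.092 / 0.076 = 1.21 times in the weak design B setting with no BA effect. With weak confounders and a true BA effect of 0.3 at N = 200, power at the 5% level was 90.0% with the fixed set against 95.1% with the p<0.05 screen. The tolerance-model sentence needs no change for this point.

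### The Sidak correction, most naturally read as single-step, could be replaced by step-down Holm-Sidak, which controls the same error and never rejects fewer hypotheses

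*Protocol article*

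**What the plan says.** The Data analysis section of the protocol article closes with a general rule: tests are two-sided at an overall 5% level, with the added clause "applying when appropriate a Sidak’s correction for multiple comparisons". It does not say whether the correction is single-step or step-down, and it does not list the tests that form the family.

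The Sample size section takes 45% of patients as frail or pre-frail and plans to show a standardised effect above 0.5 between biological age and frailty in a sample of 200, with power above 80%. The level for each comparison is given in these words: "for a two-sided type I error at 0.01 (correction due to multiple comparisons". One fixed level for every comparison is how a single-step correction works.

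On reporting, the Data analysis section says: "The results will be expressed with effect sizes and 95% confidence intervals". It does not mention multiplicity-adjusted intervals.

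**The concern.** Single-step Sidak holds every test in the family to the strictest threshold, even after some hypotheses have been rejected. The step-down version uses that threshold only for the smallest p-value and relaxes it after each rejection. If the plan means single-step, it gives up some power on the second and later findings and gains no error control in return. What is at stake is how many of the real relations between biological age and frailty are declared. The validity of the declared ones is not in question.

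**Working it through.** **Inputs from the document (Sample size section).** 200 patients, 45% frail or pre-frail, so 90 versus 110; standardised effect 0.5; two-sided level 0.01 per comparison; power above 80%. The overall two-sided 5% comes from the Data analysis section.

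**Assumptions.** The number of tests m is not given. I take m = 5, because 0.05/5 = 0.0100 (Bonferroni) and 1 − 0.95^(1/5) = 0.0102 (Sidak) both fit the stated 0.01. The correlation between tests is not given either; I use equal correlations from 0 to 0.95.

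**Step 1: reproduce the plan's figure.** Noncentrality = 0.5 × √(90 × 110 / 200) = 0.5 × √49.5 = 3.518. Power at two-sided 0.01 is 82.7% (normal) or 81.9% (noncentral t). At the Sidak level of 0.0102 it is 82.9%. The statement of power above 80% holds.

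**Step 2: thresholds for m = 5.** At step j, counting from 0, Holm-Sidak uses 1 − 0.95^(1/(5 − j)).

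| Ordered p-value | Single-step | Step-down |
|---|---|---|
| smallest | 0.0102 | 0.0102 |
| 2nd | 0.0102 | 0.0127 |
| 3rd | 0.0102 | 0.0170 |
| 4th | 0.0102 | 0.0253 |
| largest | 0.0102 | 0.0500 |

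The first row is identical, so the required sample size does not change. No later step-down threshold is stricter, so everything that single-step rejects is also rejected by step-down.

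**Step 3: error control.** Suppose k null hypotheses are true. When the first of them is rejected, the threshold in force is at most 1 − 0.95^(1/k). The family-wise error is therefore at most the chance that the smallest of k null p-values falls below the Sidak level for k tests. Wherever Sidak's inequality is valid, that chance is at most 5%. The condition is the same as for single-step.

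**Step 4: simulation.** 400,000 runs per setting; five equicorrelated two-sided z-tests; noncentrality 3.518 for true effects. The table gives average power per true effect, single-step to step-down.

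| True effects | Correlation 0 | 0.5 | 0.8 | 0.95 |
|---|---|---|---|---|
| 1 of 5 | 0.829 to 0.830 | 0.829 to 0.830 | 0.830 to 0.830 | 0.829 to 0.829 |
| 2 of 5 | 0.829 to 0.845 | 0.829 to 0.843 | 0.829 to 0.840 | 0.830 to 0.839 |
| 3 of 5 | 0.829 to 0.865 | 0.829 to 0.859 | 0.828 to 0.853 | 0.829 to 0.850 |
| 5 of 5 | 0.829 to 0.924 | 0.829 to 0.903 | 0.828 to 0.887 | 0.828 to 0.871 |

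With five true effects, the probability of detecting all five rises from 39% to 72% at correlation 0 and from 67% to 84% at 0.8. The probability of detecting at least one does not change (0.940 for both at 0.8).

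Family-wise error stayed below 5% for both versions in every setting. Under the global null it is the same for both: 0.050, 0.043, 0.030 and 0.019 at correlations 0, 0.5, 0.8 and 0.95.

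**The case against.** The strongest reply is that nothing here is wrong. Sidak is a valid correction, conservative when tests are positively related, and the power figure stands. The choice between two valid methods can look like taste. The text also never says single-step, and a condensed article may leave the variant and the test family to the analysis plan. All of this stands, which is why the point is only an improvement. It goes slightly beyond taste because one version dominates the other. If step-down was already intended, one added word settles the matter.

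Two stronger readings are tempting and are not supported.

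- A reader might infer that related tests are the reason to change: several clocks, with the age gap that "will be expressed as a difference and as a percentage (ratio) to assess the relevance of these two modalities". Holm-Sidak makes no use of correlation. Its gain with five true effects shrinks from 9.5 percentage points at correlation 0 to 5.9 at 0.8 and 4.2 at 0.95. Its global-null error is as conservative as that of single-step. Using the correlation would need a resampling method, and that is not clearly cheap with covariate-adjusted models that carry patient and centre random effects.
- A reader might infer that the change is free. Single-step Sidak has directly matching simultaneous intervals; step-down has no simple ones. The plan promises 95% intervals and none that are adjusted, so nothing promised is lost. Still, an unadjusted interval may exclude no effect while the adjusted p-value is not significant.

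**Conclusion.** This is a cheap improvement. If the plan means single-step, as the wording and the flat 0.01 suggest, Holm-Sidak is uniformly at least as powerful, with the same family-wise error control and the same sample size. The reason is this dominance, not the relatedness of the tests.

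With m = 5 and the protocol's own effect size, average power goes from 83% to 87-92% if all five effects are real, to about 84-85% if two are real, and does not move if one is real. The upper figures are therefore a best case.

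The size rests on the assumed m and equal correlations. The document does not define the family. Counting three clocks, each as biological age, difference and ratio, would already give 3 × 3 = 9 tests, for which these gains were not computed. The dominance itself holds for any m.

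**What to change.** In the closing sentence of the Data analysis section, replace the reference to Sidak's correction with *step-down Holm-Sidak correction*. Keep the planned 95% confidence intervals and label them as unadjusted, so that readers know why an interval and an adjusted p-value may differ.

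The cost is one phrase, one label and a standard routine. Data collection, the sample size and the first threshold are unaffected. The change should be made before the relevant results are seen, so that the method is not chosen after the fact.
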